### Sample size

2.7

Previous studies have lacked assessments using the gold standard. Therefore, we conducted a preliminary study to determine the sample size. In this study, 48 ischemic stroke patients were randomly assigned in a 1:1 ratio to the OE and NG groups, and their baseline and day 15 DOSS scores were assessed. The sample loss rate was conservatively set at 30%. Based on the results and Cohen’s formula, at least 211 participants were required for each group. The formula is as follows:

$$n1=n2=\frac{2\times {\left(Z_{\alpha {/}_{2}}+Z_{\beta }\right)}^{2}\times \sigma^{2}}{{\left(M1-M2\right)}^{2}}÷0.7$$

In this case, the corrected *α* = 0.007, (1−*β*) = 95%. M1 = 4.00, M2 = 5.16, 
σ
=2.39. The effect size was derived from our preliminary randomized trial using FEES-confirmed DOSS scores. Given the lack of prior large-scale rigorous data using gold-standard swallowing assessments, this effect size represents a clinically plausible and realistic improvement supported by our pilot data and clinical experience. This target sample size (n1 = n2 = 211) is higher than that found in related studies retrieved from common databases such as the Web of Science, PUBMED, and CNKI. Sample size calculations based on other parameters yielded results below this value. To ensure the test power, these results were not adopted. The sample sizes in other scenarios are shown in Appendix S5.

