**Methods:**

This multicenter randomized controlled trial will include 422 ischemic stroke patients with dysphagia who require tube feeding. Stratified randomization will be performed to assign participants 1:1 to the oro-esophageal or nasogastric groups. All participants will receive 15-days routine rehabilitation care and nasogastric or oro-esophageal feeding, according to their group assignment.

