### Statistical methods

2.9

Generalized Estimating Equations will be used to analyze repeated measures data, including the baseline and outcome DOSS, MSS, YPR-SRS, and PAS. The analyzed effects will include time, between-group, and interaction terms. Significant interaction effects indicate that differential interventions can impact the outcomes over time. Based on the primary outcome, additional analysis will be conducted by comparing the intergroup differences in the proportion of participants who will achieve oral intake at T1, using the chi-square test. The time to improvement of one level from the baseline DOSS and the time to oral intake will be analyzed using stratified log-rank tests, with stratification by the baseline DOSS. Data from patients who do not achieve their goals will be censored at day 42. The number of overt aspiration per person over 6 weeks will be analyzed using negative binomial regression to assess intergroup differences in incidence rates. Kaplan–Meier analysis will be used to handle the occurrence of aspiration pneumonia and to plot survival function curves. Statistical analyses will be based on intention-to-treat, and multiple imputation methods will be used to address partial missing values (31). Furthermore, we plan to perform several sensitivity analyses, including per-protocol analysis using a sample that excludes dropouts, and exclusion of centers from different geographic regions, to explore the stability of the main findings. The significance level *α* has been adjusted to 0.007 based on the number of outcomes (Bonferroni). Statistical analyses will be conducted using Stata v18.0 MP.

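### The sample-size formula in section 2.7, with its own inputs, gives 229 per group (458), not 211 (422); at the planned 30% loss, 422 gives about 93% power, not 95%.

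*Protocol article*

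**What the plan says.** Section 2.7 (Sample size) of the protocol article bases the calculation on a 48-patient preliminary randomised study. It prints a normal-approximation formula for two means with Z at alpha/2, and divides the result by 0.7. The inputs follow: corrected alpha 0.007, power 95%, "M1 = 4.00, M2 = 5.16" and a standard deviation of 2.39. On attrition it says "The sample loss rate was conservatively set at 30" per cent. The result is given as "at least 211 participants were required for each group".

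The Methods part of the abstract carries the doubled figure: "This multicenter randomized controlled trial will include 422 ischemic stroke patients with dysphagia who require tube feeding". Section 2.9 (Statistical methods) confirms the 0.007 significance level as a Bonferroni adjustment for the number of outcomes. Appendix S5, which is not shown, is cited for sample sizes in other scenarios.

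**The concern.** The formula and all its inputs stand in one section, so any reader can check the result, and the check fails. The protocol calls 211 per group a minimum, and section 2.7 says that smaller results from other parameters were set aside to protect power. If the adopted number is itself below what the formula requires, the 95% power attached to the primary outcome is not delivered under the plan's own assumptions. The figure of 422 in the abstract then rests on the same error.

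**Working it through.** **Inputs (section 2.7; alpha also in 2.9).** Two-sided alpha = 0.007, so z(0.9965) = 2.697. Power 95%, so z(0.95) = 1.645. Difference = 5.16 − 4.00 = 1.16. SD = 2.39. Loss 30%, applied as ÷0.7. Allocation 1:1.

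**Step 1: try to reproduce 211 with the printed formula.**

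n = 2 × (2.697 + 1.645)² × 2.39² / 1.16² ÷ 0.7

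- (2.697 + 1.645)² = 18.85
- 2 × 18.85 × 5.7121 / 1.3456 = 160.04 evaluable per group
- 160.04 / 0.7 = 228.63, so 229 per group and 458 in total

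Rounding up to 161 before dividing gives 161 / 0.7 = 230. The total of 422 is correctly 2 × 211, so the discrepancy lies in the 211. The gap is 229 − 211 = 18 per group (36 in total), or 18 / 211 = 8.5%.

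**Step 2: look for another reading that gives 211.**

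| Variant | Per group after loss |
|---|---|
| Unrounded alpha, 0.05/7 | 227.9 |
| Means and SD varied within their rounding (difference 1.15 to 1.17, SD 2.385 to 2.395) | 223.8 to 233.6 |
| One-sided alpha 0.007 | 204.1 |
| Power 90% | 192.0 |
| 160.04 × 1.3 instead of ÷ 0.7 | 208.1 |
| t-test n of 162, × 1.3 instead of ÷ 0.7 | 210.6, rounds up to 211 |

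Only the last variant reaches 211. It departs from the printed formula twice: it uses a t-based n, and it multiplies by 1.3 instead of dividing by 0.7.

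**Step 3: power at 211 per group with 30% loss.**

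- Evaluable: 211 × 0.7 = 147.7 per group
- 1.16 / (2.39 × √(2/147.7)) = 4.171
- Power = Φ(4.171 − 2.697) = Φ(1.474) = 93.0%
- By the noncentral t: 92.5% at 147 and 92.7% at 148 per group, so about 92.6%

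The type II error is therefore about 7%, against the 5% stated.

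**Step 4: difference detectable with 95% power at 147.7 per group.**

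(2.697 + 1.645) × 2.39 × √(2/147.7) = 1.21 levels, against 1.16.

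**Step 5: loss at which 211 still gives 95% power.**

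1 − 160.04 / 211 = 0.24. By the normal formula, power with 211 randomised per group is 98.9% with no loss, 97.9% at 10%, 96.1% at 20% and 93.0% at 30%.

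**The case against.** The best case for the plan is that the effect is small and conditional. The protocol calls the 30% allowance conservative. The primary outcome is measured at day 15, and section 2.2 excludes patients expected to leave or transfer within two weeks. If loss stays at or below about 24%, the trial has its 95% power. This stands as a limit on the size of the problem, and a reader should not infer that the trial lacks 95% power whatever happens. The documents give no observed loss rate, so they do not show which side of 24% the trial will fall on. But 30% is the assumption on which the protocol bases its number, and under that assumption the stated power is not reached.

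A reader might also infer that the trial was really planned at 93% power, because the formula gives 211.2 at that level. The documents do not support this: they state 95%, and 211.2 would round up to 212. A slip in the loss inflation (162 × 1.3) fits the number better, but that too is inference. Neither account removes the mismatch.

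Appendix S5 might hold further detail, but it is cited for other scenarios and cannot change what the main-text formula returns. Multiple imputation (section 2.9) does not rescue the figure either, because the protocol's own calculation counts only the 70% who remain.

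**Conclusion.** The sample size is wrong as written. With the printed two-sided alpha of 0.007, 95% power, means 4.00 and 5.16, SD 2.39 and division by 0.7, the requirement is 229 per group (458), not 211 (422). No reading consistent with the printed Z at alpha/2 and the printed ÷0.7 gives 211. At the planned 30% loss, 422 participants give about 93% power (93.0% normal, about 92.6% t), a shortfall of about two points.

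This rests on the plan's own difference, SD and loss rate, taken at face value. It shows a stated minimum that fails its own formula. It does not show a trial that is seriously underpowered.

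**What to change.** Reconcile the number with the formula in section 2.7. Keep 422 and restate the power as about 93% at two-sided alpha 0.007 for a 1.16-level difference, SD 2.39 and 30% loss. Remove the statement that 211 per group is what 95% power requires. It would help to add that 95% power is retained if loss stays at or below about 24%. The abstract's 422 can then stand. The cost is a corrected sentence or two, with no extra patients and no change to the design or analysis. If the sponsor instead wishes to keep the claim of 95% power at 30% loss, the number that matches the printed formula is 229 per group (458), which means 36 more participants.

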### Data collection and management

2.8

Assessors will be trained in advance in the Dysphagia Research Institute of Zhengzhou University to enhance consistency. In the fourth week, staff will contact participants by phone to remind them to record aspiration symptoms and the close-out timepoint of the study, to facilitate their completion of the follow-up. The database management system of the sponsor center will be used to store data. Only researchers will have access to generated documents and databases. All publicly available content will involve de-identified data. Demographic data will be stored in a separate file, which will only be accessible to the principal investigator after the study ends.

### Statistical methods

2.9

Generalized Estimating Equations will be used to analyze repeated measures data, including the baseline and outcome DOSS, MSS, YPR-SRS, and PAS. The analyzed effects will include time, between-group, and interaction terms. Significant interaction effects indicate that differential interventions can impact the outcomes over time. Based on the primary outcome, additional analysis will be conducted by comparing the intergroup differences in the proportion of participants who will achieve oral intake at T1, using the chi-square test. The time to improvement of one level from the baseline DOSS and the time to oral intake will be analyzed using stratified log-rank tests, with stratification by the baseline DOSS. Data from patients who do not achieve their goals will be censored at day 42. The number of overt aspiration per person over 6 weeks will be analyzed using negative binomial regression to assess intergroup differences in incidence rates. Kaplan–Meier analysis will be used to handle the occurrence of aspiration pneumonia and to plot survival function curves. Statistical analyses will be based on intention-to-treat, and multiple imputation methods will be used to address partial missing values (31). Furthermore, we plan to perform several sensitivity analyses, including per-protocol analysis using a sample that excludes dropouts, and exclusion of centers from different geographic regions, to explore the stability of the main findings. The significance level *α* has been adjusted to 0.007 based on the number of outcomes (Bonferroni). Statistical analyses will be conducted using Stata v18.0 MP.

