### Participants

2.2

Participants will be recruited from six rehabilitation departments across five cities in China (Suzhou, Kaifeng, Xingtai, Harbin, and Zhengzhou). The inclusion criteria are as follows: (i) Age over 18 years; (ii) First-ever stroke; (iii) Ischemic stroke based on imaging data; (iv) Enteral nutritional support is required (13); (v) Stable vital signs; (vi) Clear consciousness; and (vii) Dysphagia Outcome and Severity Scale (DOSS) level 1–2 (14); (viii) Informed consent and willingness to comply with the study procedures. The exclusion criteria are as follows: (i) Dysphagia that might be caused by other etiologies or structural abnormalities of the swallowing process; (ii) Severe hepatic, renal or hematological diseases, or malignant tumors; (iii) Contraindications to tube feeding; (iv) Pregnancy or breast feeding; and (v) Anticipated discharge or transfer to other hospitals within 2 weeks.

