### Randomization and blinding

2.3

Randomization will be performed after obtaining informed consent and completion of baseline assessments, conducted separately at each trial site hospital by independent researchers using SAS version 9.4. Stratified randomization will be performed according to the DOSS levels to randomly assign participants in a 1:1 ratio to the oro-esophageal or nasogastric groups, with a block size of 4 or 6. Randomization information will be stored in the Clinical Research Methodology Key Unit and will remain inaccessible to irrelevant people.

The interventionists and participants will be unblinded, as the feeding method is identifiable. Some assessments will be scheduled during the intervention period, and these assessors will be unblinded. The assessors for day-15 assessments will be independent and blinded, as the feeding tube will be removed after the intervention period ends.

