Psychological intervention	Communication is conducted with patients and their caregivers to identify potential psychological issues. For those with suspected psychological problems, emotional stabilization is achieved through verbal comfort, peer-to-peer communication among patients, and meditation.	Routine
Other rehabilitation	For participants with functional impairments other than dysphagia, corresponding physical therapy and occupational therapy are arranged. As for swallowing function, distinctive interventions are provided based on the equipment available at each center, such as transcutaneous electrical stimulation, music therapy, and the Rood technique. For participants with cognitive impairment, routine cognitive training is provided once daily for approximately 30 min, including memory training, attention training, and executive function training conducted under the guidance of therapists.	After swallowing behavior rehabilitation
Nutritional support	To ensure full reproducibility and cross-center consistency, both feeding interventions follow fixed, protocolized implementation rules with identical nutritional targets, positioning, insertion/confirmation, feeding frequency, volume progression, and post-feeding care.	Routine

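### Randomisation is run separately by site within DOSS level, but no test adjusts for site and the day-15 oral-intake chi-square also ignores DOSS level, so a modest gain in precision is forgone

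*Protocol article*

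**What the plan says.** **Design.** Section 2.2 has patients "recruited from six rehabilitation departments across five cities in China", with DOSS level 1 or 2 at entry. Section 2.3 says randomisation is "conducted separately at each trial site hospital by independent researchers using SAS version 9.4". It continues: "Stratified randomization will be performed according to the DOSS levels to randomly assign participants in a 1:1 ratio", "with a block size of 4 or 6". Allocation is therefore balanced within site as well as within DOSS level, giving 6 × 2 = 12 cells.

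**Analysis (section 2.9).**
- DOSS, MSS, YPR-SRS and PAS: a GEE with baseline and day-15 values both as responses. "The analyzed effects will include time, between-group, and interaction terms"; no site or stratum term is named.
- Oral intake at day 15: a chi-square test, with no stratification.
- Time to one-level improvement and time to oral intake: these "will be analyzed using stratified log-rank tests, with stratification by the baseline DOSS". Site is not mentioned.
- Overt aspiration counts: negative binomial regression, with no stratum named.
- Centre appears only in a sensitivity analysis that leaves out centres by region.

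**Reason to expect site differences.** Table 1 in section 2.4 says that, for swallowing function, "distinctive interventions are provided based on the equipment available at each center".

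**The concern.** Blocking within site and DOSS level forces the arms to be balanced on both. If those factors predict the outcome, the treatment difference varies less from trial to trial than an unstratified formula assumes. An analysis that leaves them out keeps their variance in the residual: standard errors come out too large, tests reject less often than their nominal level, and the benefit of the blocking is not used.

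The plan is also uneven. It treats baseline DOSS as a stratum for time to oral intake but not for the proportion with oral intake at day 15. Section 2.5.2 defines oral intake as DOSS level 3 or above, so the entry level fixes how far a patient has to move.

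Omitting centres in a sensitivity analysis shows whether one region drives the result. It does not remove between-site variance from the main estimate.

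**Working it through.** **Inputs (section 2.7).** Two-sided α = 0.007, so z = 2.697; power 95%; means 4.00 and 5.16, difference 1.16; SD 2.39 with no covariate adjustment; 211 per arm; 30% loss, hence 211 × 0.7 = 147.7 evaluable per arm. The between-site share of variance, R², is not given anywhere, so I take 5%, 10% and 20% as assumptions.

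**The plan's own figure.** The printed formula gives 160.04 evaluable per arm, and 160.04 / 0.7 = 228.6, so 229 rather than 211. That is a separate matter. Here it only sets the starting point:

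SE = 2.39 × √(2/147.7) = 0.278; power = Φ(1.16/0.278 − 2.697) = 93.0%.

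**Effect of omitting site.** With allocation balanced by site, the true SE is 0.278 × √(1 − R²), while the unadjusted analysis still reports about 0.278.
- SE inflation: 1/√(1 − R²)
- True size: 2 × [1 − Φ(2.697/√(1 − R²))]
- Unadjusted power: Φ((1.16 − 2.697 × 0.278)/(0.278 × √(1 − R²)))
- Adjusted power: Φ(1.16/(0.278 × √(1 − R²)) − 2.697)

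| R² (assumed) | SE too wide by | True size of a 0.007 test | Power unadjusted | Power adjusted | Gain |
|---|---|---|---|---|---|
| 0 | 0% | 0.0070 | 93.0% | 93.0% | 0 |
| 5% | 2.6% | 0.0057 | 93.5% | 94.3% | 0.8 |
| 10% | 5.4% | 0.0045 | 94.0% | 95.5% | 1.5 |
| 20% | 11.8% | 0.0026 | 95.0% | 97.5% | 2.5 |

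The comparison must be made within a row. Setting each adjusted figure against 93.0% would overstate the gain, because blocking by site also raises unadjusted power.

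**Simulation.** Six sites, two DOSS levels, blocks of 4 or 6, 296 evaluable patients, baseline slope 1; 6000 null and 3000 power runs per setting. Power for the group-by-time contrast versus the adjusted model was 94.1% vs 93.9% (site share 0), 94.8% vs 95.5% (5%), 95.3% vs 96.6% (10%) and 96.4% vs 98.0% (20%). Null rejection of the unadjusted contrast fell from about 0.007 to about 0.004. The direction and rough size agree with the table.

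**DOSS level in the primary GEE.** Baseline DOSS is a response, so the group-by-time term compares changes from it. Entry at levels 1–2 caps the baseline SD at about 0.5. The variance of a change contrast relative to a baseline-adjusted one is (2.39² + 0.5² − 2ρ × 0.5 × 2.39)/(2.39² × (1 − ρ²)). This is 1.044 at ρ = 0, 1.012 at 0.1, 1.000 at 0.2, 1.009 at 0.3 and 1.113 at 0.5. The power lost is at most 1.4 points over these values (98.3% vs 96.9% at ρ = 0.5).

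**DOSS level in the chi-square.** Assume equal numbers at each level, with 40% of level-1 and 70% of level-2 entrants reaching oral intake. Total variance is 0.55 × 0.45 = 0.2475; within-level variance is (0.24 + 0.21)/2 = 0.225. The share explained is 0.0225/0.2475 = 9.1%, so the SE is 4.9% too wide and the true size is 0.0047.

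**Would main effects be enough?** Not for the GEE interaction. With two complete timepoints and an identity link (assumed; none is named), time-constant covariates do not affect that contrast. In a simulated data set with site explaining 20% of day-15 residual variance, the interaction estimate was 0.8143 with robust SE 0.2911, with or without site and baseline-DOSS main effects. Only terms crossed with time changed the SE, to 0.246.

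**The case against.** The strongest reply has four parts.

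1. **The error is on the safe side.** There is no bias and no inflated type I error. This stands.
2. **The sample size uses an unadjusted SD,** so an unadjusted analysis keeps at least the power that calculation implies. This stands too. A reader might infer that power falls below plan because of this omission; the documents do not support that. The gap between 93.0% and the stated 95% comes from the sample-size arithmetic.
3. **The primary GEE is less exposed than it looks.** A reader might infer that it ignores the DOSS stratum, but baseline DOSS is in its response. Site differences that are constant over time also cancel in the interaction; only differences in recovery matter. Table 1 makes those plausible, but core swallowing rehabilitation and feeding rules are standardised and no between-site variance is reported.
4. **Covariates are often left to an analysis plan,** and the stated GEE terms are not said to be exhaustive. This stands in part for the GEE and the negative binomial model. It does not cover the chi-square, which cannot take a covariate, or the log-rank tests, whose stratification factor is stated. The chi-square is, however, labelled an additional analysis, which limits what is at stake there.

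**Conclusion.** The point holds as a matter of efficiency and consistency. The article fixes an allocation balanced by site and DOSS level, then names no test that adjusts for site and one test, the chi-square, that ignores both factors. If site explains 5% to 20% of the variance in the analysed outcome, the forgone power is about 0.8 to 2.5 points and the actual size of a nominal 0.007 test is 0.0057 to 0.0026. If sites do not differ in recovery, nothing is lost on that account.

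This rests on assumed variance shares, a normal approximation to an ordinal scale, 30% loss, and reading separate randomisation at each hospital as separate allocation lists. It is not grounds for calling any planned test invalid.

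**What to change.** - **DOSS, MSS, YPR-SRS, PAS:** model the day-15 value on group, its own baseline value, baseline DOSS level and site. For DOSS, the baseline value and the entry level are the same variable, so it enters once. Alternatively keep the GEE and add site-by-time terms for all four scales, plus baseline-DOSS-by-time terms for MSS, YPR-SRS and PAS. Main effects alone will not do it.
- **Oral intake at day 15:** replace the chi-square with a Cochran–Mantel–Haenszel test stratified by baseline DOSS and site, or an adjusted logistic model reported with a risk difference.
- **Time-to-event outcomes:** stratify the log-rank tests by site as well as baseline DOSS.
- **Overt aspiration counts:** add site and baseline DOSS level to the negative binomial model.

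The cost is wording only, since site and baseline DOSS are already recorded. Twelve cells for 422 patients average about 35 each (422/12). Cells with few patients or events will contribute little to the stratified tests, which is a small price. Fixing the terms before unblinding also removes a later choice between adjusted and unadjusted results.
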